**Methods:**

The study will be conducted in four phases: (1) development of DEDIKASI-app, (2) questionnaire development for an awareness study, (3) acceptability testing, and (4) effect measurement of DEDIKASI-app. We will adopt design thinking methodology to develop the app, involving systematic reviews, expert consultations, focus group discussions, and validation of the questionnaire on skin disease awareness. We will recruit 50 members of the community for the awareness and acceptability study and 1 health care worker per community health center to assess their perception of the app. A pilot study will assess the acceptability of DEDIKASI-app among community members and health care workers based on various constructs, with responses categorized as positive, negative, or undecided. The validity and reliability of a newly developed questionnaire on skin disease awareness will be tested, with validity results analyzed qualitatively and reliability measured using Cronbach α. The effectiveness of DEDIKASI-app in improving community awareness will be evaluated through a randomized controlled trial, using total scores, means, and SDs for control and intervention groups. Statistical significance of awareness level changes will be determined by delta change (*P* value), with *P*<.01 considered significant.

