### Phase 4: Randomized Controlled Trial of the Effectiveness of DEDIKASI-App to Increase Early Detection of Skin Diseases Including Leprosy

The fourth phase is an randomized controlled trial aimed to assess the effectiveness of DEDIKASI-app as a strategy to increase awareness and early detection of leprosy and other common skin diseases.

The sample size will be calculated using the following formula for hypothesis testing for 2 population means (2-sided test) [33]:

The following values will be used: level of significance (α)=5%; power of the test (1-β)=90%; population SD (σ)=5; and population variance (σ^2^)=25. The population mean (µ_1_) will be obtained after the awareness study in the second phase; as there was no previous study available, µ_2_ represents the anticipated population mean of the intervention group. Sample size will be calculated afterward; however, we will expect to obtain 600 participants.

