### Statistical Analysis

Results of validity and reliability testing of the community awareness questionnaire developed in phase 2 will be analyzed using both descriptive and analytical statistics. Demographic data will be analyzed descriptively, while the validation and reliability of the questionnaire will be assessed statistically using Pearson correlation and Cronbach α, respectively. Content and face validity will be qualitatively used to avoid question item ambiguity, ensure clarity and relevancy, and ensure that the questions are not judgmental, intrusive, or distressing to target participants [34]. The questionnaire will be administered through an interview setting, with all selected respondents interviewed at 2 points: a preintervention interview and a postintervention interview conducted approximately 4 weeks later (during the intervention study in phase 4).

During the third phase, the questionnaire developed in phase 2 will be used to collect the data on awareness in the general community. All responses to the questions will be given numerical scores based on correct or positive answers. The total score will be calculated, while the mean range will be used to illustrate the distribution and variation of scores. To measure the impact of the intervention, the change in scores (delta change) between preintervention and postintervention assessments will be calculated for each group. The Wilcoxon signed-rank test will be used to compare paired preintervention and postintervention scores within each group. A *P* value of <.01 will be considered statistically significant, indicating improvements in respondents’ knowledge, prevention practices, and health-seeking behavior.

The acceptability test for DEDIKASI-app will be conducted during the third phase, using a survey based on the TAM. A Likert scale will be used as a scoring system. The results from both community members and HCWs will be descriptively analyzed and presented using a frequency table.

Data from the randomized controlled trial in the fourth phase will be analyzed using SPSS version 21 (IBM Corporation). We will conduct a descriptive analysis by calculating the either the mean or median values of the awareness scores and the count of reported common skin disease cases through DEDIKASI-app. The choice between mean or median will depend on the distribution of the scores. We will also use a box plot diagram to visually compare the measurements between the 2 groups.

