For assessing the effectiveness of DEDIKASI-app as an intervention for enhancing awareness compared to the control group, we will apply an independent sample *t* test if the data exhibit a normal distribution. If the data distribution is not normal, we will use the Mann-Whitney test. All statistical analyses will be performed at a significance level of .05, with a 95% CI (or using the IQR if medians are used).

Missing data will be described and explored. We acknowledge that incomplete case analysis can introduce bias and will consider appropriate imputation techniques during final analysis depending on the extent and pattern of missingness. We will include the outcomes of all participants (intention-to-treat), regardless of the extent the intervention group used DEDIKASI-app.

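### The between-arm test, summary and interval depend on a normality check of the outcome data, so the trial may end without an estimate of the mean difference in its own sample size formula

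*Protocol article*

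**What the plan says.** For the comparison of the app with control, the Statistical Analysis section prescribes an independent-samples t "test if the data exhibit a normal distribution". It continues: "If the data distribution is not normal, we will use the Mann-Whitney test". The descriptive analysis of the trial data follows the same logic: "The choice between mean or median will depend on the distribution of the scores". The sentence that sets the 0.05 level for all analyses makes the interval switch as well: "with a 95% CI (or using the IQR if medians are used".

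Elsewhere the article speaks of means. The Phase 4 section takes its sample size from a "formula for hypothesis testing for 2 population means", two-sided, with "level of significance (α)=5%; power of the test (1-β)=90%; population SD (σ)=5". The abstract says effectiveness will be evaluated "using total scores, means, and SDs for control and intervention groups", and that significance will be judged on the delta change.

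The article does not say how normality is judged, whether per arm or pooled, or whether on the post score or the change. It gives no score range, no allocation ratio and no difference in means. The sample size calculation is deferred, and 600 participants is an expectation. The Current Progress section says that data collection has finished and analysis is under way.

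**The concern.** The outcome data choose the question. A t test addresses the difference in mean awareness. A Mann-Whitney test addresses whether a person in one arm tends to score higher than a person in the other, which is not a statement about means unless the two distributions differ only in location. Which of the two the trial reports is unknown until the scores are examined, and on the published account those scores are already in hand.

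The interval matters most. An IQR describes how individual scores spread within an arm. It does not narrow as the sample grows and is not an interval for a treatment effect. If the median branch is followed as written, the main result is a P value beside two medians with IQRs, with no estimate of the app's effect and its uncertainty.

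**Working it through.** **Inputs.** From the Phase 4 section: two-sided alpha 0.05, power 0.90, SD 5, 600 people expected. Assumed, because the article does not give them: 300 per arm; integer total scores with a maximum between 20 and 100; mean at 50% to 80% of the maximum; independent participants.

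**1. The plan's figure.** 600 cannot be reproduced, because no difference in means is given. Solved backwards:

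difference = (1.960 + 1.282) × 5 × √(2/300) = 3.242 × 5 × 0.0816 = 1.32 points, or 0.265 SD.

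Differences of 1, 1.5 and 2 points would need 1052, 468 and 264 people in total. Unequal arms hardly matter: a 286 to 314 split gives 1.325.

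**2. Does the t test need normal scores here?** Simulated on bounded integer scores, 300 per arm:

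| | t test | Mann-Whitney |
|---|---|---|
| Type I error, identical distributions | 0.047–0.056 | 0.045–0.056 |
| Power at a difference of 1.32 | 0.89–0.91 | 0.88–0.99 |

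The two-stage rule (check normality, then choose the test) had type I error of 0.045 to 0.056. With the difference present, the t test and Mann-Whitney reached different conclusions in 1.4% to 8.3% of simulated trials.

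**3. Which branch would be taken?** Chance that at least one arm fails a normality test at the 0.05 level:

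- Kolmogorov-Smirnov with Lilliefors correction: 97% to 100% in every scenario.
- Shapiro-Wilk: 100% on short scales or with scores near the ceiling, but 38% to 60% on many longer or well-centred scales.
- Change score (one arm, assumed pre-post correlation 0.5): Lilliefors 85% to 100%, Shapiro-Wilk 23% to 64%.

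The branch therefore depends on a check and a score range that the article does not name.

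**4. What the interval becomes.** For scale only, take a roughly normal score with SD 5. The 95% CI for the mean difference has half-width 1.960 × 5 × √(2/300) = 0.80, so width 1.6 points. The IQR within an arm is 1.349 × 5 = 6.7 points wide at any sample size. The two are not alternatives to each other.

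**The case against.** **Detail left to a fuller plan.** An article need not define a normality criterion, and its absence is no fault by itself. The sentence on mean or median belongs to a descriptive analysis. Both points stand. But the switch of the between-arm test and the replacement of the CI by an IQR are stated rules, not omissions.

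**Mann-Whitney is a sound test and often the more powerful one.** This stands. On skewed scores it frequently beat the t test. It can also lose: if 20% of the app arm gained 6.6 points and the rest nothing, power was 86% for t and 80% for Mann-Whitney. Power favours neither branch in general.

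**A reader might infer that the rank test would declare the app effective, or harmful, when mean awareness is equal.** With equal means and unequal spread, Mann-Whitney rejected in 12%, 56% and 79% of simulated trials (SD 5 vs 3.5, 5 vs 3, 4.5 vs 3), while the Welch t test stayed at 5%. This shows that Mann-Whitney does not test means, but nothing in the article points to such a pattern. Partial use of the app would not produce it: if users gain and non-users do not change, the mean rises too. In the 20% example the mean moves by 0.2 × 6.6 = 1.32, and the SD only from 5 to √(25 + 0.2 × 0.8 × 6.6²) = 5.7.

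**Clustering matters more.** This stands. Health centres were randomised, and step 2 ignores that. With about 30 people per centre and an assumed intracluster correlation of 0.01, the design effect is 1 + 29 × 0.01 = 1.29, and a nominal 5% test rejects in about 8% of null trials (1.96/√1.29 = 1.73). At 0.05 the design effect is 2.45 and the figure about 21%. Either test is affected. This is a separate problem, but the fix must not ignore it.

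**Conclusion.** The point holds in a limited form. The rule as written can leave the trial with a test that does not address the difference in means in its own formula and abstract, and with no interval for the app's effect. In return it offers little protection, because at this size a comparison of means does not depend on normal scores.

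Three stronger readings are not supported:

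- That the scores are almost certain to fail the check. This depends on an unnamed test and an unstated range.
- That the trial was sized for a particular mean difference. Only the formula is fixed.
- That the switch inflates type I error or costs power in general. Simulation shows no inflation under identical distributions, and power can go either way.

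The t-test figures rest on 300 independent people per arm, SD 5 and bounded integer scores. They show that non-normality is not the obstacle, not that an unadjusted t test is valid for this cluster-randomised trial. The change is worth making: it is a moderate fault with a cheap remedy.

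**What to change.** In Statistical Analysis, delete the normality switch for the between-arm comparison. State that the effect is the difference between arms in mean awareness score with its 95% CI, whatever the distribution, estimated by a method that allows for the randomised health centres. Name the score (post or change) so that it agrees with the delta change in the abstract. Keep medians, IQRs, box plots and a rank test as descriptive or sensitivity results, and remove the IQR as a substitute for the CI.

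The cost is a paragraph of wording, and this point alone needs no change in sample size. Because data collection has ended and analysis has begun, this replaces a published rule late. Report it as a dated change, made before the between-arm results are seen if that is still possible, and otherwise say that it was made afterwards. One small downside: the mean is a less natural summary if scores pile up at the ceiling, which the descriptive medians would still show.

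### If medians are used, the plan literally puts the IQR in place of the 95% CI, leaving the between-arm effect without a measure of precision (minor, conditional on non-normal scores)

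*Protocol article*

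**What the plan says.** All of this is in the protocol article.

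- **Statistical Analysis, descriptive part for the phase 4 trial.** Awareness scores are summarized by mean or median, with a box plot for the two groups. "The choice between mean or median will depend on the distribution of the scores".
- **Statistical Analysis, comparison with control.** For effectiveness, "we will apply an independent sample *t* test if the data exhibit a normal distribution". Otherwise: "If the data distribution is not normal, we will use the Mann-Whitney test".
- **Next sentence, same paragraph.** "All statistical analyses will be performed at a significance level of .05, with a 95% CI (or using the IQR if medians are used".
- **Phase 4, sample size.** The formula is for "hypothesis testing for 2 population means (2-sided test", with "level of significance (α)=5%; power of the test (1-β)=90%; population SD (σ)=5". About 600 participants are expected. The effect size is left until after the awareness study.

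The article names no interval for a between-arm difference on the median or Mann-Whitney route other than through the bracket.

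**The concern.** A 95% CI for the between-arm difference says how precisely the app effect is known, narrows as the sample grows, and corresponds to a two-sided test at .05. An IQR marks the middle half of individual scores in a single arm. It has no confidence level, settles at a fixed width as the sample grows, and describes one group and not a contrast between two. Offering it as the alternative to a CI treats spread between people as if it were uncertainty about an effect.

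An analyst who followed the sentence on the non-normal route would report a P value, two medians and two IQRs. The reader could subtract the medians but could not judge how precisely the difference is known. Whether the trial's effectiveness aim is answered with an interval at all would then depend on a distribution check.

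**Working it through.** **Inputs.** Two-sided alpha .05, power 90% and SD 5, all from the Phase 4 section. Total 600, also from there. Assumed here: 300 per arm (the article gives no ratio for participants), normal shape, and no clustering except where stated.

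**1. The plan's own figure.** The 600 cannot be reproduced because no effect size is given. Solved backwards, 300 per arm gives 90% power for a difference of

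5 × √(2/300) × (1.960 + 1.282) = 1.32 points.

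This serves below only as a reference size of effect.

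**2. Width of a 95% CI for the difference in means.** Half-width = 1.96 × 5 × √(2/300) = 0.80, so the full width is 1.60 points.

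**3. Width of the IQR in one arm.** 2 × 0.6745 × 5 = 6.74 points. The ratio to the CI width is 6.74 / 1.60 = 4.2.

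**4. Behavior as the sample grows.**

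| Per arm | 95% CI width for the difference | IQR width in each arm |
|---|---|---|
| 100 | 2.77 | 6.74 |
| 300 | 1.60 | 6.74 |
| 1000 | 0.88 | 6.74 |

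The CI responds to the amount of information and the IQR does not.

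**5. Relation to the .05 test.** For two normal arms with SD 5, the IQRs separate only when the centers differ by more than 2 × 0.6745 × 5 = 6.74 points, about five times the reference difference (6.74 / 1.32 = 5.1). In 500 simulated trials with a true shift of 1.32 points, the Mann-Whitney test was significant in about 89%, and the arms' IQRs overlapped in every one.

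**6. What a proper interval on the rank route looks like.** In the same simulated trials, the 95% CI for the Hodges-Lehmann shift averaged 1.64 points wide and covered the true shift in about 94%. The average IQR was 6.69 points.

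**7. Clustering.** CHCs were randomized. With 600 / 21 = 28.6 participants per CHC, the half-width is multiplied by √(1 + 27.6 × ICC). The article gives no ICC. At assumed values of 0.01 and 0.05 the half-width becomes 0.90 and 1.23, or full widths of about 1.8 and 2.5. The interval widens but stays well short of the IQR.

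**The case against.** **The bracket may be descriptive.** It is triggered by the use of medians, not by the use of the Mann-Whitney test, and so echoes the mean-or-median rule in the descriptive part. Median with IQR is the ordinary summary for skewed scores, and the sentence never says what quantity its CI is for. On this reading only an unnamed estimator would be left, which an article may leave to the full protocol or analysis plan. The possibility stands and is a reason to keep the point small. It does not remove it. The descriptive plan already has its own place; the bracket follows directly on the two tests, is tied to the significance level, and is worded as the alternative to a CI. That is a wrong substitute in print, not an omitted detail, and even if description was meant the sentence needs correcting.

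**Stronger readings that a reader might infer, and that the article does not support:**

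- *That the .05 comparison is invalidated.* The P value comes from the test and does not depend on what is printed beside it.
- *That the size of the effect could not be read.* Both medians would be reported, so their difference is visible; its precision is what is missing.
- *That overlapping IQRs would be taken as no effect.* The plan draws no inference from overlap and decides by the test.
- *That the median route is the likely one.* The article gives no score range, number of items or expected shape.

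**The figures use normal data for a branch that applies only to non-normal data.** This is correct. They illustrate how the two quantities differ and do not predict this trial's results. The difference in kind does not depend on the shape of the scores.

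**Conclusion.** The point holds as a minor one. Taken as written, the sentence replaces an interval for the app effect with a within-arm spread whenever scores are judged non-normal, and on that route the effectiveness result would carry no valid measure of precision. The sample size, the data and the Mann-Whitney P value are unaffected by this wording. The size of the mismatch, a CI about 1.6 points wide against an IQR of about 6.7, rests on the plan's SD of 5 together with an assumed 300 per arm, normal shape and no clustering. It is an illustration and not an estimate of harm. If the scores turn out to be normal, the bracket never comes into play.

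**What to change.** In the Statistical Analysis section:

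1. Delete the bracket about the IQR from the sentence on the significance level.
2. State that the between-arm effect is reported with a 95% CI whichever test is used.
3. Name one estimand for the rank-based route, for example the Hodges-Lehmann shift. Do not leave a choice between that and a difference in medians: the two can differ for skewed scores, and the Mann-Whitney test is not in general a test of medians.
4. Let the interval and the test allow for randomization by CHC through the same method, suited to 21 clusters. A cluster-based interval beside a test that ignores clusters could disagree with it, and a bootstrap that resamples CHCs may cover poorly with so few.
5. Move the IQR to the descriptive part, as the within-arm companion to the median.

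The cost is a few sentences and a little more analysis code, possibly outside SPSS version 21, and a wider interval once clustering is allowed for. No new data are needed. The Current Progress section says that data collection has ended and analysis is underway, so the change should be made and recorded before results are reported.

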### Ethical Considerations

Ethical clearance for the study (all 4 phases) has been sought from the Ethical Review Board of the Faculty of Public Health Universitas Airlangga, Surabaya, with registration number 160/EA/KEPK/2023. The trial in phase 4 has been registered to the INA-CRR, the trial study registry of the Ministry of Health, Republic of Indonesia (INA-O8EX278). Paper-based informed consent will be asked from all participants. Participants will be informed during the consent process whether they will be allocated to the intervention or control group. As such, participants will be aware of whether or not they will be using DEDIKASI-app. This may have influenced their expectations.

All participant data collected via DEDIKASI-app will be stored securely with encryption and password protection. Only authorized HCWs will have access to identifiable information through the HCW interface. Study participants will be informed of data confidentiality, and in case of health concerns, they may be referred to their nearest CHC for follow-up. Research assistants and HCWs involved in the study will receive training on privacy, communication protocols, and referral procedures.

## Results

### Current Progress

This study received ethical clearance from the Ethics Review Board of the Faculty of Public Health, Universitas Airlangga (160/EA/KEPK/2023) and is registered in the Indonesia Clinical Research Registry (INA-O8EX278). Field research was funded by NLR Indonesia and Erasmus MC for the period of May 2022 to December 2024. At the time of manuscript submission, phase 1 (DEDIKASI-app development) and phase 2 (questionnaire validation) had been completed. Data collection for the randomized controlled trial has recently concluded, and data analysis is currently underway. Final study results are expected to be published by the end of 2025.

### Phase 1: Development of DEDIKASI-App

The app will be developed following the design thinking methodology, incorporating literature reviews, expert consultations, and focus group discussions. The final version of the app will be validated by a panel of health care professionals and community members to ensure its usability and relevance.

### Phase 2: Awareness Study and Questionnaire Development

A questionnaire will be developed and validated to measure awareness levels of common skin diseases. It is expected that initial results will show varying levels of awareness among different demographic groups, with the highest awareness likely among HCWs. Statistical validation will be conducted to confirm the reliability and accuracy of the questionnaire.

